### Overall Measures

#### Demographics

We will collect demographic information from the RANI sample, including age, education, number of children, and caste or tribe membership.

#### mIFA Measures

##### Self-efficacy for IFA Adherence

Self-efficacy in adhering to an IFA regimen was conceptualized as the extent to which women feel confident that they can continuously take IFA when facing a number of relevant barriers. At baseline, we asked the participants the extent to which they agreed they (1) could take IFA every week when not pregnant, (2) believed they could easily take IFA, (3) could take IFA even if their husband or father does not want them to, and (4) could take IFA even if their mother-in-law or mother does not want them to. Responses were coded on a 5-point Likert scale and averaged into a scale for self-efficacy for adherence at baseline.

We will measure self-efficacy for adherence at the end line using a modified scale that includes additional barriers for adherence. Participants will be asked the extent to which they are confident they (1) will continue to take IFA every day (for pregnant women) and every week (for nonpregnant women), (2) are anemic, (3) are not anemic, and (4) receive advice from others to discontinue taking IFA. Barriers were identified during the formative research phase of the RANI project [7]. Women will also be asked the extent to which they are confident they can take IFA every day if they are pregnant (or every week if they are not pregnant), as these are the recommended doses for this population. The four items will be answered on a 5-point Likert scale, ranging from *strongly disagree* to *strongly agree*. Scores will be averaged into a scale for self-efficacy to adhere to IFA at the end line.

#### IFA-Related Social Norms

The RANI project operationalizes three forms of social norms: descriptive, injunctive, and collective. This study conceptualizes IFA-related descriptive norms as the extent to which women believe others regularly consume IFA. At baseline, women were asked, “what proportion of a) non-pregnant, b) pregnant and c) adolescent girls take IFA regularly?” Responses were recorded as *none*, *some*, *about half*, *most*, or *all* and averaged into a three-item scale for descriptive norms related to IFA. Similar questions will be asked at the end line. Women will also be asked new descriptive norms questions at the end line related to adherence: “How many a) non-pregnant, b) pregnant c) adolescent girls do not miss a dose or two of IFA?” and “How many a) non-pregnant, b) pregnant and c) adolescent girls continue to take IFA even after missing a dose or two?”

IFA-related injunctive norms were conceptualized as the extent to which women believe others expect them to consume IFA regularly. At baseline, women were asked, “how many women in your community think you should take IFA tablets regularly if you are pregnant?” as well as if they are not pregnant. Responses were recorded on the same scale as descriptive norms, ranging from *none* to *all*. In addition, women were asked the extent to which they agreed that their (1) mothers-in-law (or mothers) and (2) husbands (or fathers) think they should take IFA regularly if they are pregnant, as well as not pregnant. Responses were recorded on a 5-point Likert scale ranging from *strongly disagree* to *strongly agree*. All responses were averaged into a 6-item scale for injunctive norms related to IFA use. Similar measures will be collected at end line. Similar to descriptive norms, women will also be asked new injunctive norms questions at the end line relating to adherence. We will ask women, “Do you agree that your a) mother-in-law (or mother) and b) husband (or father) will think badly of you if you miss a dose?”

Previous studies have conceptualized collective norms as the prevalence of a focal behavior within a community [47], and it has been operationalized as the mean of the behaviors of everyone in one’s community except that of the referent person, also called the *nonself mean* [48,49]. For the mIFA arm, we will operationalize collective norms as the prevalence of nonself mean of self-reported adherence to IFA supplements within a cluster, weighted by the number of women in the cluster who are also in the mRANI arm.

#### mBI Measures

##### Bystander Self-efficacy to Prevent Violence Against Women

This study conceptualizes bystander self-efficacy as the extent to which women feel confident in their ability to intervene when they witness another woman experiencing violence. At the end line, we will ask women the degree to which they agree with 8 statements stating, “If I witness violence against a woman, I am confident I could intervene by distracting (e.g. beating pots and pans); delaying (e.g. checking in after witnessing violence with the victim); delegating (e.g. seeking help from SHG group members or influential community leaders); documenting the violence (e.g. calling a hotline or recording on a cell phone) as a bystander.” Responses will be scored on a 5-point Likert scale, ranging from *strongly disagree* to *strongly agree*, and averaged into an eight-item measure for bystander self-efficacy to prevent violence against women.

##### Violence Against Women–Related Social Norms

Violence against women–related descriptive norms were conceptualized as the extent to which women believe that others intervene when witnessing violence in their community. We will measure descriptive norms by asking participants to report how many women in their community and friends would intervene if they saw a woman experiencing violence. Responses will be recorded as *none*, *some*, *about half*, *most*, or *all* and averaged across the two items.

Violence against women–related injunctive norms were conceptualized as the extent to which women believe that others expect them to intervene if they witness a woman experiencing violence. This study will operationalize these injunctive norms by asking participants the extent to which they agree with the following statement: “If you saw a woman experiencing violence, [referent] will expect you to intervene,” in which the referent will be (1) most women in the community, (2) most friends, and (3) most women in self-help groups. We will record responses on a 5-point Likert scale ranging from *strongly disagree* to *strongly agree* and average them across the two items.

The operationalization of violence against women–related collective norms will mirror the mIFA arm, except that we will use intentions to engage in bystander intervention strategies in lieu of behaviors [48,49]. As such, for the mBI arm, we will operationalize collective norms as the prevalence of nonself mean intentions to engage in bystander intervention strategies within a cluster, weighted by the number of participants in the cluster who are also in the mBI arm.

### Process Evaluation

Prior EE interventions leveraging IVR systems have reported success in their ability to facilitate and track audience engagement in real time and at scale [50]. Following their lead, monitoring of the mRANI intervention delivery and receptivity will occur in real time. Textbox 2 summarizes process evaluation measures and indicators for mRANI. Data on intervention dose, audience attention and involvement or engagement, character identification, narrative satisfaction and engagement, and perception of the most important problem in their village at the end of the EE program will be autogenerated by the IVR system immediately upon episode release and delivery. Process evaluation measures and indicators gauging recall and interpersonal communication related to mRANI will also be measured during the end line assessment.

Mobile reduction in anemia through normative innovations process evaluation indicators.
**Dose**
Number of calls sentNumber of calls receivedNumber of entertainment education (EE) episodes heard in full by the mobile reduction in anemia through normative innovations (mRANI) participants
**Audience involvement or engagement**
Number of interactions with interactive componentsNumber of likes on episodesNumber of replays of episodesNumber of calls and queries on the mRANI hotlineNumber of referrals to community and clinical linkages
**Attention**
Number of seconds spent listening to episodesNumber of seconds spent relistening to episodesNumber of seconds spent listening to jinglesNumber of seconds spent listening to episode teasersNumber of seconds spent listening to episode recaps
**Recall**
Percentage of participants who accurately recall prosocial themes addressed in the episodesPercentage of participants who accurately recall mRANI charactersPercentage of participants who accurately recall major mRANI plot points
**Narrative satisfaction and engagement**
Percentage of participants engaged with the narrativePercentage of participants satisfied with the narrative
**Character identification**
Percentage of participants who identify with Malati (protagonist) or Dolly (protagonist’s daughter)
**Most important problem in the village**
Percentage of participants who identify anemia or violence against women (depending on their assignment) as the most important problem at the end of the mRANI EE program

### Ethical Considerations

#### Research Ethics Approval

The full RANI trial, including the mHealth intervention, has been reviewed and approved by appropriate institutions in the United States and India. These institutions include the George Washington University institutional review board in the United States; the Sigma Science and Research in New Delhi, India; and the Indian Council for Medical Research’s Health Ministry’s Screening Committee. The trial has also been registered with the Clinical Trial Registry of India.

#### Participant Orientation, Consent, and Confidentiality

Participants will be contacted with preintervention delivery for validation of phone numbers, followed by orientation and enrollment. The orientation and enrollment activities will take place a week before the mRANI intervention delivery commences. A structured script will be prepared to orient potential participants to mRANI and inform them of the objectives and intervention delivery channel and duration. For participants who express interest in enrolling in the mRANI study, we will obtain verbal informed consent. Next, we will note their preferences for the day and time to receive the mRANI EE programs. Participants will also receive contact information for additional questions and feedback.

#### Risk Mitigation Plan

Given the short duration and digital delivery format of this intervention, we anticipate low levels of exposure to adverse events for mRANI participants. In addition, considering that the mRANI educational messages are strategically masked within an entertaining narrative tested in the field, we expect minimal sensitivity and negative reactions from our audience or their family members. However, the study team acknowledges that violence against women is a sensitive subject matter in Angul, Odisha. The mRANI study will adhere to the risk mitigation plan in place for the larger RANI trial [2]. Enrolled mRANI participant names and their data will be documented in an encrypted file. To maintain confidentiality, only 1 team member will have access to these data. To prevent unintended consequences for potential mRANI participants, the study team limited intervention delivery to women who are phone owners; thus, they have more agency and privacy related to their phone use. In addition, special consideration will be given to the delivery of EE programs during the day and time selected by the participant to ensure their privacy and security. The name of the mRANI study will appear on the caller ID when delivering new episodes so that participants and their family members will not face ambiguity tied to the source of the EE programs. Community and clinical referrals will be provided to participants who call the mRANI hotline. Local experts and consultants will triage requests beyond the scope and sphere of influence of the mRANI study. Finally, participants will have the option to opt out of mRANI EE programs at any time by contacting the mRANI hotline or by pressing 0 on their phone.

### Statistical Analysis

The primary analyses planned for the mRANI impact evaluation will test the hypotheses that participants assigned to the treatment arm will have higher levels of self-efficacy in IFA adherence (primary end point) and self-reported IFA use (secondary end point) at follow-up and that participants assigned to the control arm will have higher levels of bystander self-efficacy for prevention of violence against women. We will test these three hypotheses in three ways. First, because participants are randomized to treatment and control groups, a simple comparison of those groups should produce an unbiased estimate of the treatment effect. Therefore, we will estimate, for each end point, the linear regression model *Yij = b1 + b2 × TREATij + eij*, where *i* indexes the individual participant, *j* indexes the study cluster, and *b2* is the treatment effect. We will estimate this model by using ordinary least squares regression but use robust standard errors to test the null hypothesis (H_0_: b1=0) because of the nesting of participants in study clusters.

Although these analyses should produce unbiased estimates of treatment effects, they may miss key opportunities to increase statistical power and precision through two analytic elaborations. The first is to introduce cluster fixed effects to the model, which effectively results in a within-cluster comparison of the treatment and control group participants. As treatment assignment is within clusters, cluster and treatment assignments are orthogonal, so the addition of cluster fixed effects should increase statistical power and precision by reducing the residual error variance. In this case, the analytic model for each end point will be *Yij = aj + g1 × TREATij + eij*, where *aj* is a vector of cluster fixed effects, and *g1* is the treatment effect. As with the first modeling approach, we will estimate this model using ordinary least squares; however, in this case, the inclusion of cluster fixed effects obviates the need to use robust SEs.

Another opportunity to improve statistical power while retaining unbiased estimation is to control for pretreatment variables that are likely to be highly correlated with the primary and secondary end points. These include measures of the same variables taken before randomization: baseline and midline self-efficacy for serum hemoglobin levels, IFA adherence, and IFA use. Note that bystander self-efficacy for violence against women was not measured at baseline or midline and thus cannot be included as a covariate. In addition, sociodemographic variables assessed at baseline and midline, such as age, education, and parity, can also be considered for inclusion. We will choose covariates for inclusion based on their marginal associations with each end point. The resulting model for each end point will be *Yij = aj + d1 × TREATij + Xij × h + eij*, where *aj* is once again a vector of cluster fixed effects, *Xij* is a vector of select control variables assessed at baseline and midline, and *d1* is the treatment effect. As with the second modeling approach, we will estimate this model using ordinary least squares with no need for robust SEs.

This approach will produce three estimates of the treatment effect for each end point: b1, g1, and d1. All are unbiased, and we expect them to be similar across the three specifications. The main difference we expect would be in the SEs, which we expect will be highest in the first and lowest in the third specification. For transparency, we will report the estimates from all three specifications for each end point.

To assess the extent to which social norms and interactivity mediate the relationship between intervention exposure and primary outcomes in both mIFA and mBI arms, we will use a structural equation model to estimate the effects of the intervention on the mediator variables, the effects of the mediators on the 2 self-efficacy variables (IFA use and bystander intervention), and the direct effect of the treatment arm on both self-efficacy variables. From this model, we will estimate the percentage of the intervention effect on each aspect of self-efficacy mediated by each of the mediators [51]. All analyses will be performed using Stata (StataCorp) for Windows, version 14.2 [52].

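### Model 1 defines b2 as the treatment effect, but its null hypothesis and the list of reported effects name b1, the intercept

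*Protocol article*

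**What the plan says.** All of this is in the Statistical Analysis section of the protocol article.

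- Model 1 is Yij = b1 + b2 × TREATij + eij, fitted by ordinary least squares for each end point. Its gloss reads "and *b2* is the treatment effect".
- For that model the plan will "use robust standard errors to test the null hypothesis (H_0_: b1=0) because of the nesting of participants in study clusters".
- Model 2 adds cluster fixed effects: Yij = aj + g1 × TREATij + eij, "and *g1* is the treatment effect".
- Model 3 adds covariates: Yij = aj + d1 × TREATij + Xij × h + eij, "and *d1* is the treatment effect".
- The summary of the three models reads "This approach will produce three estimates of the treatment effect for each end point: b1, g1, and d1". The symbol b2 does not appear in it.

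The models are introduced with "We will test these three hypotheses in three ways", and none of the three is named as primary. The Abstract describes the between-group comparison as ordinary least squares with robust standard errors. Of the three models, only model 1 uses them; the text says models 2 and 3 do not need them.

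**The concern.** In model 1 as written, b1 is the expected outcome when TREAT=0 and b2 is the difference between arms. The null hypothesis and the reporting list both point to b1. Nothing in the article redefines b1 as the treatment coefficient.

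This is the only null hypothesis the article writes out, and it belongs to the specification that matches the Abstract. Model 1 is fitted for every end point, so the mismatch applies to IFA self-efficacy, IFA use and bystander self-efficacy alike. Anyone who programs from the text, or checks published results against it, would be looking at the wrong row of the regression output. They would then report an arm mean as an effect.

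**Working it through.** **Symbols side by side**

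| Model | Coefficient of TREAT | Named in the text as the effect | Null hypothesis written out | In the reporting list |
|---|---|---|---|---|
| 1 | b2 | b2 | b1=0 | b1 |
| 2 | g1 | g1 | none | g1 |
| 3 | d1 | d1 | none | d1 |

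Only model 1 is inconsistent.

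**Inputs**

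- Sample Size section, taken from a cited study: treatment mean 3.30 (SD 0.68), control mean 2.89 (SD 0.6), power 0.8, α .05, 39 per arm.
- Results section: 192 women in the IFA arm and 189 in the control arm at end line.
- Self-efficacy for IFA Adherence section: "The four items will be answered on a 5-point Likert scale, ranging from *strongly disagree* to *strongly agree". The numeric coding is not given.

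**Step 1. Which parameter is the trial sized for?** The pooled SD is √((0.68² + 0.6²)/2) = 0.641 and the difference is 3.30 − 2.89 = 0.41. The two-sided formula gives n = 2 × 0.641² × (1.960 + 0.842)² / 0.41² = 38.4, so 39 per arm. The plan's figure reproduces. It is a calculation for the difference between arms, which is b2 in model 1.

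**Step 2. What would be reported?** With the cited values, b1 = 2.89 and b2 = 0.41, so the listed quantity would be about seven times the arm difference (2.89/0.41 = 7.0).

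**Step 3. What would the written test do?** Ignoring clustering, the statistic for b1=0 is 2.89/(0.6/√189) = 66.2. This shows scale only, because the plan specifies robust standard errors.

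**Step 4. Simulation with cluster-robust standard errors.** There were 189 and 192 women, with 40 clusters and an intracluster correlation of 0.05 (both assumed), SD 0.641, and 1,000 runs per row.

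| Coding and control mean | True effect | Rejects b1=0 | Rejects b2=0 |
|---|---|---|---|
| 1 to 5, mean 2.89 | 0 | 100% | 5.9% |
| 1 to 5, mean 2.89 | +0.41 | 100% | 100% |
| 1 to 5, mean 2.89 | −0.41 | 100% | 100% |
| 0 to 4, mean 1.89 | 0 | 100% | 5.7% |
| −2 to +2, mean −0.11 | 0 | 55.5% | 6.0% |
| −2 to +2, mean 0 | 0 | 6.6% | 5.8% |

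If IFA use is taken as a binary end point with no effect (500 runs each, outcomes drawn without a cluster effect), b1=0 is rejected in 49.8% of runs at a control rate of 2%, 98.2% at 5%, and 100% at 10% and 30%.

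The rejection rate for b1=0 follows the coding and the control-arm level. On the 1 to 5 coding it is the same for no effect, benefit and harm.

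**The case against.** The best defence is that the intention is clear. The article introduces model 1 as a plain comparison of the randomised groups. It calls all three listed quantities treatment effects, expects them to agree closely, and expects their standard errors to shrink from the first model to the third. An intercept near 2.9 could not agree with g1 and d1 near 0.41. The sample size is also for an arm difference. There may be only one slip: if the equation and its gloss had used b0 + b1 × TREATij, the null hypothesis and the reporting list would both be right as printed, and b1 would match g1 and d1 in style. All of this stands. It settles what was meant, but it leaves the printed null hypothesis wrong for the printed model.

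A reader might infer more than the article supports:

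- **That the primary test is invalid.** No specification is designated primary, and two of the three are labelled correctly. What can be said is that the affected model is the one matching the Abstract.
- **That the test always rejects.** This depends on a coding the article does not give. It holds in the simulations with 1 to 5 and 0 to 4 coding, but not with coding centred on zero or for a rare binary end point.
- **That the type I error is 100%.** Rejecting b1=0 when the control mean is 2.89 is a correct rejection of a false null. It becomes a false claim only if the intercept is then presented as an effect.

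**Conclusion.** The point holds as an error of notation in an analysis rule. Taken literally, model 1's test and reported estimate concern the TREAT=0 arm mean and say nothing about the intervention. The gap between the two quantities is about 2.89 against 0.41. That comparison rests on the cited study's means, which need not describe this trial's control arm, and on an all-positive coding of the 5-point items. The conclusion that b1 is not the treatment effect needs neither assumption, nor the assumed cluster count and correlation. The context makes the intended parameter clear, and g1 and d1 are unaffected. The article does not show that the analysis itself was programmed wrongly.

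**What to change.** Make the symbols consistent in one of two ways:

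1. Keep the equation, change the null hypothesis to H0: b2=0, and list the three estimates as b2, g1 and d1.
2. Rewrite model 1 as Yij = b0 + b1 × TREATij + eij, name b1 as the treatment effect, and leave the null hypothesis and the list as they are.

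In either case, confirm that the analysis code tests and reports the coefficient of TREAT for each end point. The cost is a few changed symbols and a short code check. Design, sample size and data collection are not affected.

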**Methods:**

Mobile reduction in anemia through normative innovations (mRANI) is a randomized 2-arm study that includes assessments before and after the intervention. All study participants will be recruited from the intervention arm of the parent reduction in anemia through normative innovations trial only. Although the usual practice is to randomize participants either to a treatment arm or a usual care control arm, we will assign the mRANI control group to another entertainment education–based treatment group that is designed to improve bystander intervention to reduce violence against women. Data collection for the mRANI study is embedded in the parent trial and will include baseline and end line assessments. The primary outcomes are self-efficacy for IFA adherence and violence against women–related bystander intervention. The inclusion criteria for the mRANI study are participation in the parent trial and phone ownership. Women (approximately n=400) who meet the mRANI inclusion criteria will be randomly assigned to the IFA arm or the bystander arm. Ordinary least squares regression with robust SEs will be conducted to assess between-group comparisons at the end line. A mediation analysis will be conducted to examine whether social norms and interactivity mediate the relationship between intervention exposure and primary outcomes in both arms. Real-time monitoring data will offer insights into intervention receptivity and audience engagement.

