### Sample Size

We calculated the required sample size based on the findings of Constantino et al [46] in which they observed an improvement in self-efficacy in the treatment group (mean 3.30, SD 0.68) that was higher than that in the control group (mean 2.89, SD 0.6; *P*<.001). On the basis of similar assumptions, with a power of 0.8 and α of .05, our required sample size was 39 participants in each arm, which was rounded up to 40. To account for the subanalyses that we will conduct based on participants’ caste (tribal, scheduled caste, and other), we increased the sample size to 40×3=120 participants in each arm, for a total of 240 participants.

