### Data Collection

The mRANI study data collection will be embedded within the overall RANI trial, similar to its intervention delivery strategy. Women between the ages of 15 and 49 years residing in treatment (n=2061) and control (n=2049) clusters have been recruited and randomly selected to participate in the impact evaluation of the RANI project. Baseline survey of the RANI participants took place in September 2019, and an end line survey was scheduled to take place in February 2021. Baseline data collection for the larger RANI project served as formative data toward developing the mRANI EE programs and segmenting potential participants. The study team will conduct the impact evaluation for the mRANI study using data from end line assessments, controlling for baseline estimates.

The average time to complete a survey during the baseline and midline data collection was 55 minutes for all RANI measures and outcomes. The mRANI-specific modules take an average of 15 minutes to complete. Translation and back translation of the entire survey instrument, including mRANI-specific modules, will be conducted to check the accuracy of the questionnaire’s translation. Pretesting of mRANI-specific modules will be conducted in nonsampled villages to ascertain reliability and appropriateness in this intervention context. A description of the data collection methods for the parent trial can be found in the parent trial’s protocol [2].

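### Three models per end point, none named as decisive: when their p-values disagree the plan has no pre-stated answer, and a claim resting on any one of them would carry a false-positive rate of about 8–12%

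*Protocol article*

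**What the plan says.** Statistical Analysis in the Protocol article introduces the primary analyses and lists three hypotheses: IFA self-efficacy (primary end point), self-reported IFA use (secondary end point) and bystander self-efficacy. Each is to be tested with three models:

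- Model 1: end-line score on arm, ordinary least squares with robust standard errors.
- Model 2: arm plus cluster fixed effects, without robust standard errors.
- Model 3: model 2 plus selected baseline and midline covariates.

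For model 3 the rule is "We will choose covariates for inclusion based on their marginal associations with each end point". No threshold or procedure is given, and the sociodemographic candidates are introduced only as examples. The section expects similar estimates from the three models, with the largest standard error in the first and the smallest in the third. It closes: "For transparency, we will report the estimates from all three specifications for each end point".

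Two other places describe the analysis in the singular. The abstract says "Ordinary least squares regression with robust SEs will be conducted to assess between-group comparisons at the end line". Data Collection says that the impact evaluation uses end-line data, "controlling for baseline estimates".

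**The concern.** The article sets out the testing scheme in full, with equations and standard-error choices, and gives the three models equal standing. It does not say which result settles a hypothesis or what happens if they disagree. The abstract describes model 1, since models 2 and 3 explicitly drop robust standard errors. Data Collection describes model 3, since models 1 and 2 contain no baseline term.

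Two things are at stake. First, if one model gives p below 0.05 and another does not, the trial has no pre-stated answer for that end point. Second, if the conclusion may follow whichever model is significant, the error rate is no longer the 5% on which the sample size rests. The open covariate rule adds a further choice inside model 3.

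**Working it through.** **1. The plan's own figure.** Sample Size gives means 3.30 and 2.89, SDs 0.68 and 0.60, and "with a power of 0.8 and α of .05, our required sample size was 39 participants in each arm". The difference is 0.41 and the mean variance is (0.68² + 0.60²)/2 = 0.4112 (SD 0.641). Then n = 2 × (1.960 + 0.842)² × 0.4112 / 0.41² = 38.4, rounded up to 39 per arm. The figure reproduces with two-sided α = 0.05, so the sample size is not at issue. No error rate across models is stated.

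**2. Can the models disagree?** Adding a covariate with outcome correlation r multiplies the standard error by about √(1 − r²): 0.954 at r = 0.3 and 0.866 at r = 0.5. Take one estimate with a test statistic of 1.80 without the covariate (p = 0.07). At r = 0.5 it becomes 1.80/0.866 = 2.08 (p = 0.04). The same estimate then gives two verdicts, through the standard-error difference that the article itself expects.

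**3. Error rate under the null.** From the document: 381 women, 192 and 189 per arm (Results), and one unstratified random list (Randomization). Assumed, because the article does not give them: 15–80 clusters, ICC 0.02–0.15, main covariate coefficient 0–0.7, and 6–20 candidate covariates. Model 1 used cluster-robust standard errors. Model 3 screened covariates at p < 0.05. There were 4,000 simulated trials per setting, with a Monte Carlo standard error of about 0.3 points at a 5% rate.

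| Decision rule | False-positive rate per end point |
|---|---|
| Model 1 alone | 4.6–6.3% |
| Model 2 alone | 4.6–5.7% |
| Model 3, screened at p < 0.05 | 4.6–5.8% |
| Model 3, fixed covariate list | 4.7–5.8% |
| Any of the three significant | 7.6–11.7% |

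Three independent tests would give 1 − 0.95³ = 14.3%. The simulated figure is lower because the estimates are correlated. A second simulation (2,000 trials per setting, 30–90 clusters, ICC 0.05, baseline coefficient 0.3, 12 noise covariates screened at p < 0.10) gave 7.9–9.5% for any of three.

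**4. What the covariate rule adds.** With pure-noise candidates (10 or 30, screened at 0.05 or 0.20), the arm test rejected in 4.8–5.5% of trials. A fixed screen that ignores arm therefore does not inflate the error. If the threshold may be picked afterwards from 0.01, 0.05, 0.10 and 0.20, model 3 alone rejects in 6.3–6.9%, and any of three in 9.6–12.6%.

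**The case against.** The article commits to reporting every estimate, so selective reporting is excluded, and it states no rule that any significant model counts as success. That stands, and it makes the 8–12% conditional. But reporting all three only makes a disagreement visible. It does not resolve it, and nothing prevents the conclusion from following the favourable model.

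It can also be said that models 2 and 3 are introduced as refinements of a first model that the abstract also names, which hints at a base model. The hint is not a designation, and Data Collection points the other way. An analysis plan that is not at hand may name one model; the article would then only need to be aligned with it.

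If the effect were as large as Sample Size assumes, the models would hardly disagree: 0.41 / (0.641 × √(2/189)) = 6.2 standard errors at 189 per arm, ignoring clustering. The problem bites for smaller effects or none.

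Three stronger readings are tempting but unsupported:

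- *Screening covariates on the outcome inflates the error by itself.* It does not: under a fixed rule the rate stays near 5%. Only the open threshold and list add to it.
- *The baseline score may be dropped, losing 5–13% in standard error.* That gain belongs to r = 0.3–0.5. With 381 women, a covariate with r = 0.3 passes a p < 0.05 screen with probability 0.99997: atanh(0.3) × √378 = 6.02, less 1.96, is 4.06. Dropping it becomes likely only near r = 0.1, where the gain is 0.5%.
- *The trial-wide rate is 15–18%.* This combines two primary outcomes, taken as independent: 1 − 0.9215² = 15.1% and 1 − 0.9055² = 18.0%. One model per outcome would already give 1 − 0.95² = 9.8%. That part is ordinary two-outcome multiplicity, which choosing a model leaves untouched.

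**Conclusion.** The point holds as a badly fixed decision scheme. Three models share primary standing, two other sections point to different ones, and the article itself expects their precision to differ. A reader might infer that the plan as such runs at 8–12%. The documents do not support that, because each model alone holds about 5%. The roughly 1.5- to 2.3-fold rate applies only if a claim may rest on any one of the three. Its size depends on the assumed number of clusters, ICC and covariate strength. The absence of a pre-stated answer when the models disagree depends on no assumption. The estimates themselves remain usable.

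**What to change.** Before analysis, name one primary specification per end point. One workable choice is the article's third model, keeping the cluster fixed effects and replacing selection by marginal association with a fixed list:

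- IFA self-efficacy: baseline and midline self-efficacy.
- IFA use: baseline and midline IFA use.
- Bystander self-efficacy, which has no baseline: age, education, parity and caste.

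Label the other two specifications as sensitivity analyses that do not decide the hypothesis, and still report them, so the transparency is kept. Align the abstract and Data Collection with the choice. In the same edit, name the coefficient tested: the first model defines b2 as the treatment effect, but the null is written for b1. Because the end-line data are already in hand, record that the choice was made before any comparison by arm was seen.

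The cost is wording only, as the article lists all these measures as collected. A fixed list gives up any small precision gain from data-driven selection.
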